### **3.2 Comparative treatment regimes**

Two different treatment regimes of Metvix® PDT in patients with clinical superficial and nodular BCC will be compared.

### **3.3 Randomization and blinding**

Lesions will be randomized to either treatment regime 1 or 2 after having signed the informed consent form and having received treatment by light. An independent, blinded dermatologist with no knowledge about the randomisation for treatment will do the evaluation of the lesions after 3 months, 1 and 3 years.

### **3.4 Study flow chart**

For study flow chart, see **page 20**

### **3.5 Description of Investigational Drug**

Metvix® 160 mg/g cream is supplied in 2 g collapsible tubes. The strength is given as the concentration of the active entity, methyl-aminolevulinate, which is present as the hydrochloride. The colour of the cream is cream to pale brown.

Commercial cream will be used, and the information given in the packaging will be applicable. The cream is not specially prepared for this study.

The cream will be used in the clinics only

### **3.6 Drug Ordering and Storage**

The cream will be stored securely in a refrigerator at 2-8°C.

Metvix® 160 mg/g cream will be supplied free of charge to the patients.

### **3.7 Study Duration**

The patients will be asked to participate in the study for 3 years. Active treatment is given one to two times during a 3-month period. The follow-up visits occur at pre-fixed times during the 3 years period after treatment. Each patient will be followed for 3 years with regards to efficacy parameters and 3 months with regard to adverse events.

### 3.8 Trial Timetable

The anticipated timetable for the trial is the following: New timetable necessary

|                         |         |
|-------------------------|---------|
| Start of recruitment    | Q1 2012 |
| End of recruitment      | Q3 2012 |
| Last treatment          | Q4 2012 |
| End of 1 year follow-up | Q4 2013 |
| End of 3 year follow-up | Q4 2015 |

## 4. Patient and lesion selection

### 4.1 Number of lesions

277 patients with 374 lesions will be included.

### 4.2 Patient Screening

Eligible patients will be informed about the possibility to participate in this study. Before any trial related procedures are performed, the patient must be thoroughly informed about the study and he/she must sign and date the informed consent form.

### 4.2 Inclusion Criteria

Patients

- Males or females above 18 years of age.
- Written informed consent.

Lesions

- One or more primary histologically verified BCC, clinically assessed as of either superficial or nodular type.

### 4.3 Exclusion Criteria

Patients

- Woman with child-bearing potential
- Patients with Gorlin's syndrome, porphyria, xeroderma pigmentosum, history of arsenic exposure or known allergy to MAL
- Concomitant treatment with immunosuppressive medication
- Patients with physical or mental conditions that most likely will prevent them from attending the follow-up visits

Lesions

- Located within the mid-face-H-area
- Longest diameter >15 mm on face and scalp, >30 mm on the trunk and >20 mm on the limbs
- Any clinically evaluated pigmented or morpheaform lesions
- Any lesions with prior treatment

## **4.4 Patient Withdrawal**

Completion or trial termination for any reason will be fully documented in the CRF page.

Patients are free to withdraw from the trial at any time without providing reason(s) for withdrawal and without prejudice to further treatment. The reason for withdrawal may be withdrawal of consent, treatment failure, adverse event(s) or loss to follow-up. The reason(s) will be recorded in the CRF.

Patients who withdraw will not be replaced.

Patients withdrawing from the trial should be encouraged to go through the same final evaluations as patients completing the trial according to the protocol with special focus on safety. The aim is to record data in the same way as for patients who complete the trial. Otherwise data will be recorded as having been consented by the patient. This will be recorded in the patient notes.

# **5. TREATMENT PROCEDURE**

## **5.1 Pre-treatment Evaluation**

Pre-treatment evaluation at visit 1 will only be performed after the patient has agreed to participate and has signed and dated the informed consent form. No treatment will be initiated before the signed consent has been given.

Pre-treatment evaluation will be performed according to inclusion and exclusion criteria.

## **5.2 Randomisation and Emergency Code**

Lesions will be randomized to treatment regime 1 or 2 after treatment by light. In case of multiple BCC, the investigator will number the lesions. The first lesion will be randomized and the next lesion will get the other regime, implying that every second lesion is randomized. The coordinating investigator will supply the randomization code. This is an open study and no emergency code will be required.

## **5.3 Pre-treatment preparation**

The treatment area will be defined and marked on a chart and/or photographed, defining each lesion relative to “landscape markers” (i.e. eyebrow, ear etc.) for easier localization at later visits.

Each lesion will be numbered and recorded in the CRF.

Preparation of the lesion surface prior to PDT is a common practice and is believed to contribute to an enhanced penetration of the cream in skin. When performing curettage using a sharp curette, superficial hard keratotic tissue is removed.

The surface of every BCC lesions with 5 mm of the surrounding tissue of normal appearance will be prepared using a small dermal curette. The curettage will be performed by scraping in a checked pattern for optimal removal of scales and crusts, and to roughen the surface of the lesion. Thicker lesions require debulking.

## 5.4 Photodynamic Therapy with Metvix® 160 mg/g cream and Aktilite® (red light)

Upon having prepared the treatment area through curettage, Metvix® 160 mg/g cream will be applied as a 1-mm thick layer on the entire treatment area. The area is covered with a plastic film and on the outside with an occlusive bandage. The cream is left for 3 hours before removed and the treatment area exposed to light using light from light-emitting diodes (Aktilite®) with a light dose of 37J/cm^2 and the exposure time 7-9 minutes

A corresponding treatment session is carried out after 1 week in patients randomized to treatment regime 2. For patients in treatment regime 1; an assessment of treatment response is carried out 3 months after the initial treatment session and only lesions showing non-complete response will be given a second treatment session.

## 5.5 Drug Accountability

Each investigator will be responsible for drug accountability. For each patient treated, the batch number of the tube used must be documented.

## 5.6 Follow Up Evaluation

### 5.6.1 Efficacy follow-up

Treatment response will be assessed at the follow-up visits; 3, 12 and 36 months after treatment. The localization of the treatment sites will be made from the body chart made and the photos taken at baseline.

### 5.6.2 Safety follow-up

In case of any adverse event patients should take contact with their G.P. or the local hospital for further consultation. Adverse event will be recorded in the CRF at the follow-up visits if related to treatment, according to the investigator

Follow-up:

| Treatment regime/ lesions                                                              | Follow-up/ months after treatment  |
|-----------------------------------------------------------------------------------------------|-------------------------------------------|
| Regime 1/ all lesions                                                                         | 3 months after 1 treatment session        |
| Regime 1/ lesions with non-complete response 3 months after first session with a re-treatment | 3 months after 2 treatment session        |
| Regime 1/ all lesions in complete response                                                    | 12 months after 1 or 2 treatment sessions |
| Regime 1/ all lesions in complete response                                                    | 36 months after 1 or 2 treatment sessions |
| Regime 2/ all lesions                                                                         | 3 months after 2 treatment session        |
| Regime 2/ all lesions in complete response                                                    | 12 months after 2 treatment sessions      |
| Regime 2/ all lesions in complete response                                                    | 36 months after 2 treatment sessions      |

## 5.7 Patient Compliance

Healthcare professionals in the clinic perform the entire treatment. The cream will be applied to the entire treatment area and 5 mm of the surrounding tissue of normal appearance. Within 3 hours after cream application; the lesion will be exposed to red light using a lamp with light-emitting diodes (Actilite®) for 7-9 minutes.

# 6. ASSESSMENT OF EFFICACY

## 6.1 Lesion Response

The primary objective of this study is to record BCC lesions response rate to two different treatment regimes using MAL-PDT.

Lesions response rate is defined as number of lesions in clinical complete response at follow-up. Follow-up will occur 3, 12 and 36 months after treatment and is fully described under section 5.6.2. In the case of lesions of clinical non-complete response, a histological investigation will be carried out. Patients with histologically remaining BCC will be excluded from the study.

The investigators will be asked to assess whether each lesion response fits into one of the following two categories:

|                                        |                                                                                                            |
|----------------------------------------|------------------------------------------------------------------------------------------------------------|
| Complete response (CR):         | Complete disappearance of the lesion, visually and by palpation (mild erythema /pigmentation might remain) |
| Non-complete response (Non-CR): | Remaining lesion                                                                                           |

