## Statistics

Simple tabulation as well as logistic regression with lesion recurrence (yes/no, a binary variable) at 3 years will be employed to analyze the outcome. As one patient may yield more than one lesion, a mixed effects model with patient identity as random factor will be considered. Different lesions within the same patient will be subject to stratified randomization. The expected cure rate at 3 years (reference) is set to 80 %. The study aims to detect an experimental success rate of no less than 70 % (the non-inferiority margin 10 %). With a sample size of 170 lesions per group, a difference between the two treatment regime groups of at least 10% can be found with a significance level of 5% and a power of 80%.

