## **1.2 Benefits and Risks**

Metvix® PDT is an approved and marked treatment modality for patients with pre-malignant disease and BCC.

General benefits of topical Metvix® PDT include:

- Non-invasive treatment available on an outpatient basis
- Several separate lesions can be treated simultaneously
- The same lesion(s) can be treated repeatedly with success
- Excellent cosmetic results
- No known toxicity or interaction with other medication
- Lesion selective, leaving the surrounding tissue intact
- No skin photosensitization after 24 hours
- Only minor, manageable local side effects related to treatment site

Study benefits include the following:

If the effect of the new, alternative and simpler treatment regime proves as effective as the standard approved regime MAL-PDT will be an even more attractive therapy alternative for low-risk BCC. The treatment will be easier to manage with improved cost-effectiveness as well as reduced discomfort and fewer side effects for the patients.

The risks attributed to Metvix® PDT are few and related mainly to transient discomfort and pain during and shortly after illumination. Inflammation following tumour destruction may give local, transient erythema and oedema. Treatment of large lesions may cause severe erythema, followed by ulceration. These side effects normally last for a few days, in rare occasions up to a week after treatment.

Standard Metvix® PDT in BCC is today given as two treatment sessions separated by one week. Patients with non-complete response after one PDT session in treatment regime 1 are offered an additional PDT at the 3-month control. The possible delay of the second session of BCC treatment is acceptable, as BCC grows very slowly

Patients with non-complete response after either PDT treatment regimes at the control visit 3 months after the latest treatment session are withdrawn from the study. They are then offered standard BCC treatment at the discretion of the dermatologist. Patients will receive detailed oral and written information about the risks of side effects. If the patients find the side effects unacceptable, they are free to withdraw from the study at any time and without any further explanation.

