### **Per-protocol (PP) efficacy population**

This population will consist of all treated BCC-lesions, except lesions considered not evaluable due to major deviations from the protocol. Major deviations may include: inclusion criteria not respected, non-available efficacy assessment, visit window discrepancy, or discrepancies from the treatment schedule. Major deviations will be assessed before start of the statistical analyses. Only observed data will be part of the per-protocol analysis. A lesion with missing response at 3-months will be excluded from the calculation of the patient response rate.

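### The per-protocol rules do not say that a lesion failing before 36 months stays in the analysis as a failure, and the exclusion that removes it is worded by patient although the lesion is the unit

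*Protocol*

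**What the plan says.** **Who leaves.** Section 6.1, on lesions that are clinically not in complete response and go to histology, says: "Patients with histologically remaining BCC will be excluded from the study". The Table 1 footnote repeats this. Section 1.2 says that patients with a non-complete response in either regime "at the control visit 3 months after the latest treatment session are withdrawn from the study". In the follow-up table under 5.6.2, the 12- and 36-month rows read "Regime 1/ all lesions in complete response" and "Regime 2/ all lesions in complete response". A lesion that failed at 3 or 12 months therefore has no scheduled 36-month assessment.

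**How the analysis treats them.** Section 8.2.1 defines the primary outcome as cure or no cure of a lesion at 3 years. The PP population starts from all treated lesions and removes those not evaluable because of major deviations, among which it lists "non-available efficacy assessment". It adds: "Only observed data will be part of the per-protocol analysis". The ITT population uses LOCF. Section 8.2.2 presents both populations and says of neither that it decides the non-inferiority test.

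**Unit.** Section 8.2.1 says that each lesion is randomised, treated and followed individually. Section 5.2 alternates the regimes across the lesions of one patient.

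**Related wording.** The synopsis statistics plan a "logistic regression with lesion recurrence (yes/no, a binary variable) at 3 years". For regime 1 at the first 3-month assessment, section 5.4 says that "only lesions showing non-complete response will be given a second treatment session".

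**The concern.** In a non-inferiority trial, an analysis that removes failures from both arms usually pulls the two cure rates together. That favours the claim the trial wants to make. If PP is computed on lesions with a 36-month assessment, the worse arm loses more of its failures, and a true loss equal to the 10-point margin can look acceptable. PP is one of two co-presented analyses, so such a result could be used to support the primary claim.

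The patient-level wording is a second route to error, and it reaches ITT as well. Suppose one lesion fails and the patient leaves. A cleared lesion in the same patient, possibly under the other regime, is then no longer examined. LOCF carries its complete response to 36 months, so a later recurrence would be counted as a cure.

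**Working it through.** **Inputs from the protocol.** Control cure 85% (8.3; the synopsis and 8.2.1 give 80%), margin 10 points (8.2.2, 8.3), two-sided 95% confidence interval (8.2.2), 170 lesions per group needed and 187 recruited (8.3), 277 patients with 374 lesions (4.1).

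**The plan's own figure.** With 85% cure in both arms, a 10-point margin and one-sided 5%, 170 per group gives 81.3% power by an exact unconditional test. The stated 80% is reproduced, and 170 is used below as the evaluable number.

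**Assumption not in the protocol.** Let g be the share of all 36-month failures that are found at 3 or 12 months and so leave before 36 months. Failures first seen at the 36-month visit are observed and stay in PP.

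**Step 1: PP cure rate if early failures drop out.** With true cure p, the observed rate is p / (1 − g(1 − p)). For g = 0.5:
- regime 1: 0.75 / (1 − 0.5 × 0.25) = 0.75 / 0.875 = 85.7%
- regime 2: 0.85 / (1 − 0.5 × 0.15) = 0.85 / 0.925 = 91.9%
- difference: −6.2 points instead of −10.

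**Step 2: false non-inferiority.** Truth is set exactly at the margin (75% versus 85%), with 170 lesions per arm, independent lesions and the same g in both arms. Non-inferiority is declared when the lower limit of the Wald 95% interval lies above −10 points (400,000 simulated trials per row).

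| g | PP regime 1 | PP regime 2 | Difference | False non-inferiority |
|---|---|---|---|---|
| 0 | 75.0% | 85.0% | −10.0 | 2.6% |
| 0.25 | 80.0% | 88.3% | −8.3 | 6.5% |
| 0.5 | 85.7% | 91.9% | −6.2 | 20% |
| 0.75 | 92.3% | 95.8% | −3.5 | 65% |

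A Newcombe interval gives 18% at g = 0.5 and 57% at g = 0.75. With 80% versus 70%, the Wald figures are 14% and 50%. If every early failure is kept as no cure, the error is 2.5% to 2.6% at every g.

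**Step 3: unequal shares.**
- g = 0.4 in regime 1 and 0.6 in regime 2: 0.75 / 0.90 = 83.3% versus 0.85 / 0.91 = 93.4%, difference −10.1, false non-inferiority 2.8%.
- The reverse: 0.75 / 0.85 = 88.2% versus 0.85 / 0.94 = 90.4%, difference −2.2, false non-inferiority 60%.

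**Step 4: PP size.** The expected number is 170 × (1 − g(1 − p)). From g = 0.75 to g = 0.25 this runs from 138 to 159 in regime 1 (170 × 0.8125; 170 × 0.9375) and from 151 to 164 in regime 2 (170 × 0.8875; 170 × 0.9625). All are below 170.

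**Step 5: cleared lesions in the same patient.** 374 − 277 = 97. If no patient has more than two lesions, there are 97 pairs, or 194 lesions. The expected number of cleared lesions whose partner failed is 194 × 0.15 × 0.85 = 25 at 15% failure and 194 × 0.20 × 0.80 = 31 at 20%. This assumes independent outcomes within a patient and that every failure is found early, so it is an upper figure.

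**The case against.** **A reader might infer that failures vanish from every 36-month cure rate.** They do not. LOCF carries a non-complete response recorded at 3 or 12 months to 36 months as a failure. For the failing lesion itself, ITT keeps its error at about 2.6% whatever g is. All the inflated rates above belong to PP.

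**A reader might infer that the protocol orders failures to be dropped from PP.** It does not say so. A lesion with a recorded, biopsied failure has been assessed. The observed-data sentence may mean only that nothing is imputed, in contrast to LOCF, and the deviation list is introduced as possible examples. This objection stands in part: dropping failures is one reading, not a stated rule. But the endpoint is status at 3 years, a lesion that has left has no assessment then, and nothing in the protocol closes off the harmful reading.

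**The size rests on g.** This stands. The protocol gives no value, and Step 3 shows that the direction depends on g being similar in the two arms.

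**Cleared lesions need not be lost.** Section 8.2.1 follows lesions individually, and the follow-up table schedules later visits for all lesions in complete response. So this is a conflict with the patient-level wording, not a settled loss.

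**Two smaller readings go too far.** Section 6.1 and the footnote, read literally, exclude a regime 1 patient with residual tumour at the first 3-month visit, whom 5.4 sends to a second session. Section 1.2 largely resolves this by tying withdrawal to the control after the latest session, so it is loose wording to reconcile. Likewise, the synopsis term recurrence does not show that never-cleared lesions are left out, because 8.2.1 and 8.2.2 use cure and response.

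**Conclusion.** The point holds for the PP analysis and for the patient-level exclusion. The protocol removes failing lesions from follow-up and does not state that they remain failures in PP. If PP is taken on lesions assessed at 36 months, false non-inferiority rises from 2.6% to about 6.5%, 20% or 65% when a quarter, half or three quarters of failures leave early. This assumes 85% versus 75% true cure, 170 evaluable lesions per arm, independent lesions and equal shares. With unequal shares of 0.4 and 0.6 it ranges from 2.8% to 60%, depending on which arm loses more.

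ITT protects the recorded failure, but since neither analysis is named decisive, that does not settle the matter. ITT is itself exposed where cleared lesions lose follow-up, for at most 25 to 31 lesions under the assumptions of Step 5.

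**What to change.** 1. In the PP and ITT definitions, state that a lesion with histologically confirmed residual or recurrent tumour after its assigned regime is complete counts as no cure at 36 months in both populations, and that such a lesion is evaluable in PP.
2. In 1.2, 6.1 and the Table 1 footnote, reword the exclusion so that it ends follow-up of that lesion only. The patient's other study lesions stay in follow-up, as 8.2.1 and the follow-up table already imply.
3. In the synopsis statistics, replace recurrence with cure or no cure over all lesions, as in 8.2.1.
4. Reconcile 6.1 and the footnote with 1.2 and 5.4 for the first regime 1 assessment. Which clinical rule applies is for the investigators.

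The cost is amendment wording. Visits for lesions in complete response are already scheduled.

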| AE                  |     |   | X  | X III  |    |    |  |
| Cosmesis            |     |   | X  | X III  | X  | X  |  |
| Biopsy              |     |   | X* | X* III | X* | X* |  |

I: Approved PDT regime with two PDT treatments one week apart

II: New PDT regime with one PDT treatment

III: New PDT regime with one PDT treatment pluss one extra PDT treatment due to non-complete response after 3- month assessment.

\*Clinically suspected recurrences will be examined by histology. Patients with histologically remaining BCC will be excluded from the study.

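### The exclusion for histologically remaining BCC in section 6.1 is not limited to a completed regime or to the lesion, so as worded it conflicts with regime 1 re-treatment in 5.4 and 5.6.2 (minor)

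*Protocol*

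**What the plan says.** **Exclusion.** Protocol section 6.1 covers the efficacy assessment. It defines the visits by reference: "Follow-up will occur 3, 12 and 36 months after treatment and is fully described under section 5.6.2". It then sets the trigger, "In the case of lesions of clinical non-complete response, a histological investigation will be carried out", and the consequence, "Patients with histologically remaining BCC will be excluded from the study". No session, visit or regime limits the last sentence. The Table 1 footnote in the Appendix has similar text: "Clinically suspected recurrences will be examined by histology. Patients with histologically remaining BCC will be excluded from the study".

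**Re-treatment.** Section 5.4 says that in regime 1, at the assessment 3 months after the first session, "only lesions showing non-complete response will be given a second treatment session". The table in 5.6.2 has a row for "Regime 1/ lesions with non-complete response 3 months after first session with a re-treatment", seen again 3 months after the second session. Further rows follow regime 1 lesions in complete response at 12 and 36 months after one or two sessions. Table 1 defines group III by "one extra PDT treatment due to non-complete response after 3- month assessment" and schedules it to week 180.

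**Intended order.** Section 1.2 states: "Patients with non-complete response after one PDT session in treatment regime 1 are offered an additional PDT at the 3-month control". It then withdraws patients who are still in non-complete response, after either regime, at the control visit 3 months after their latest session.

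**Unit.** Lesions are randomised (3.3, 5.2). Where a patient has several, 5.2 gives the next lesion the other regime. Section 8.2.1 says that lesions are randomised, treated and followed one by one. The removal rules in 1.2 and 6.1 speak of patients.

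**The concern.** A regime 1 lesion with residual tumour at the first 3-month visit meets two instructions. Section 6.1 as worded takes the patient out of the study. Sections 5.4 and 5.6.2 give the lesion a second session and keep following it. Re-treatment of such lesions is part of regime 1 as the primary objective in 2.1 describes it, so the conflict falls on the regime under test.

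The effect would also be one-sided. Regime 2 lesions have had both sessions before their first 3-month assessment, so an exclusion there comes after the regime is finished. Only in regime 1 can the rule act mid-regime. The ITT population in 8.2.1 keeps every lesion on which treatment was started and fills missing values by last observation carried forward. A regime 1 lesion removed at the first 3-month visit would therefore stand as a failure at 36 months without the second session it was assigned.

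A second issue sits in the same sentence. Because it removes patients, residual tumour in one lesion could end the 12- and 36-month follow-up of the patient's other lesions, including one on the other regime.

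**Working it through.** No figure decides this point. The check is a comparison of the provisions, followed by two conversions that show scale.

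**Step 1: does 6.1 reach the first regime 1 visit?** Section 6.1 refers to 5.6.2 for its visits. The first row of that table is all regime 1 lesions, 3 months after one session. Neither the histology sentence nor the exclusion sentence in 6.1 sets that visit apart. As worded, it is covered.

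**Step 2: what do the other provisions require for that lesion?**

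| Provision | Regime 1 lesion, non-complete response at first 3-month visit, BCC on biopsy |
|---|---|
| 6.1 | Patient excluded |
| 5.4 | Second PDT session |
| 5.6.2 table | Reassessed 3 months after session 2; if in complete response, seen at 12 and 36 months |
| Table 1, group III | Extra session, visits to week 180 |
| 1.2 | Second session offered; withdrawal only if non-complete response persists at the later control |

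The first row cannot be reconciled with the others. If 6.1 were kept together with 5.4, only clinically suspicious lesions with a negative biopsy would be re-treated and followed, while confirmed residual tumour would leave the study. That is contrary to 2.1.

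**Step 3: which reading is intended?** Section 1.2 gives the order: re-treat, reassess, then withdraw. Sections 2.1, 5.4 and 5.6.2 agree with it. The missing limit belongs in 6.1.

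**Step 4: scale per lesion.** Input: 187 lesions per group (8.3); 2 × 187 = 374, which agrees with 4.1. Each regime 1 lesion that re-treatment would have cured, but that is carried forward as a failure, lowers the regime 1 ITT rate by 1/187 = 0.0053, or 0.53 percentage points. The non-inferiority margin is 10 points (8.2.2, 8.3).

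**Step 5: how many lesions reach the decision?** The protocol gives no 3-month non-response rate after one session and no biopsy-positive rate, so the number is not derivable. As an assumption only, if 10% to 40% of 187 lesions were in clinical non-complete response, 0.10 × 187 = 18.7 to 0.40 × 187 = 74.8, or about 19 to 75 lesions, would go to biopsy. Only those with residual BCC would face the conflict, and only those that re-treatment would have cured would change the ITT rate.

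**Step 6: reach of a patient-level rule.** Inputs: 277 patients and 374 lesions (4.1).

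- Lesions per patient: 374/277 = 1.35.
- Lesions beyond the first in a patient: 374 − 277 = 97, and 97/374 = 25.9%.
- Patients with more than one lesion: at most 97, reached if each has exactly two; 97/277 = 35.0%.

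This is a ceiling on the patients in whom another lesion could lose follow-up. It is not an estimate of how many would.

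**The case against.** The best defence is that the protocol, read as a whole, already answers the question. Section 1.2 states the sequence. Regime 1 is defined by re-treatment in the synopsis, 2.1, 5.4, 5.6.2 and Table 1. Section 6.1 itself points to 5.6.2, which has a row for re-treated lesions. Section 5.4 makes the second session depend on non-complete response, which 6.1 defines clinically, and Table 1 combines the 3-month follow-up and the second treatment in one visit. Nothing makes re-treatment wait for a biopsy result, and an investigator is unlikely to apply a reading that removes most of the re-treatment in regime 1.

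Most of this stands. It shows what was intended and makes literal application improbable. It does not remove the conflict. Section 1.2 belongs to the introduction, while 6.1 is the operative efficacy section and does not refer back to it. The triggers also differ: clinical response in 1.2, histology in 6.1. Even with same-visit treatment, exclusion once the biopsy report arrives would be literally possible and would end follow-up of a lesion just re-treated.

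Three stronger readings are tempting, and the document does not support them.

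- *Table 1 contradicts itself in the same way.* The footnote begins with suspected recurrences, which presuppose an earlier complete response. The biopsy row has a separate mark for group III, which keeps re-treated patients in the study. The column positions are disturbed in the text available. The footnote is ambiguous and gives support only.
- *Affected lesions would be lost from the per-protocol analysis.* Section 8.2.1 lists what major deviations may include and has them assessed before analysis. A site following 6.1 would be obeying the protocol, so this outcome is speculative.
- *The regime 1 cure rate is biased by a known amount.* No input for such a figure exists; 0.53 points is a conversion per lesion.

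The patient-versus-lesion issue could be put down to loose usage, since the protocol elsewhere also speaks of patients randomised to a regime. But a removal rule has consequences that loose description does not, and 1.2 and 6.1 both remove patients, whereas 8.2.1 follows lesions singly.

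**Conclusion.** The inconsistency is real. Section 6.1 as worded excludes at a visit where 5.4 and 5.6.2 re-treat and continue. It is a gap in the drafting of an operative rule; a reader might infer that the design denies regime 1 its second session, but 1.2 rules that out.

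The consequence is conditional on a site applying 6.1 literally. In that case only regime 1 is interrupted, and carrying the last observation forward counts those lesions as failures at 36 months, at 0.53 percentage points for each one that re-treatment would have cured. How many there would be cannot be derived, and no shift in the cure rate is claimed. Separately, removing the patient instead of the lesion could cut short follow-up of other lesions, in at most 97 of 277 patients (35.0%).

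Severity: minor.

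**What to change.** 1. **Section 6.1:** limit the rule to histologically remaining BCC after the assigned regime is complete. For regime 1 this means 3 months after the re-treatment session, or a confirmed recurrence at 12 or 36 months. For regime 2 it means from 3 months after the second session onward.
2. **Unit:** apply the rule to the lesion. Count that lesion as a failure, take it out of further efficacy follow-up, and keep the patient's other lesions on their 12- and 36-month visits, in line with 8.2.1.
3. **Table 1 footnote:** use the same wording, for consistency.
4. **Section 1.2:** make the same change from patient to lesion in the withdrawal sentence.

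Sections 5.4 and 5.6.2 need no change. The cost is a qualifying clause in 6.1 and the footnote and a change of wording in 1.2. No patients or procedures are added, and the visits kept for the other lesions are already in the 5.6.2 schedule.
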